# The Effects of the Digital Platform Support Monitoring and Reminder Technology for Mild Dementia (SMART4MD) for People With Mild Cognitive Impairment and Their Informal Carers: Protocol for a Pilot Randomized Controlled Trial

**DOI:** 10.2196/13711

**Published:** 2019-06-21

**Keywords:** dementia, mild cognitive impairment, tablet, app, carer, eHealth, mHealth

## Abstract

**Background:**

Many countries are witnessing a trend of growth in the number and proportion of older adults within the total population. In Europe, population aging has had and will continue to have major social and economic consequences. This is a fundamentally positive development where the added life span is of great benefit for both the individual and the society. Yet, the risk for the individual to contract noncommunicable diseases and disability increases with age. This may adversely affect the individual’s ability to live his or her life in the way that is desired. Cognitive conditions constitute a group of chronic diseases that predominantly affects older people. Recent technology advancements can help support the day-to-day living activities at home for people with cognitive impairments.

**Objective:**

A digital platform (Support Monitoring and Reminder for Mild Dementia; SMART4MD) is created to improve or maintain the quality of life for people with mild cognitive impairment (PwMCI) and their carers. The platform will provide reminders, information, and memory support in everyday life, with the purpose of giving structure and lowering stress. In the trial, we will include participants with a diagnosed neurocognitive disorder as well as persons with an undiagnosed subjective memory problem and cognitive impairment, that is, 20 to 28 points on the Mini-Mental State Examination.

**Methods:**

A pragmatic, multicenter RCT is being conducted in Spain, Sweden, and Belgium. The targets for recruitment are 1200 dyads—split into an intervention group and a control group that are in usual care. Intervention group participants will be provided with a data-enabled computer tablet with the SMART4MD app. Its core functionalities, intended to be used daily at home, are based on reminders, cognitive supporting activities, and sharing health information.

**Results:**

Inclusion of participants started in December 2017, and recruitment is expected to end in February 2019. Furthermore, there will be 3 follow-up visits at 6, 12, and 18 months after the baseline visit.

**Conclusions:**

This RCT is expected to offer benefits at several levels including in-depth knowledge of the possibilities of introducing a holistic multilayered information and communication technology solution for this group. SMART4MD has been developed in a process involving the structured participation of PwMCI, their informal carers, and clinicians. The adoption of SMART4MD faces the challenge of this age group’s relative unfamiliarity with digital devices and services. However, this challenge can also be an opportunity for developing a digital device tailored to a group at risk of digital exclusion. This research responds to the wider call for the development of digital devices which are accessible and affordable to older people and this full scale RCT can hopefully serve as a model for further studies in this field.

**Trial Registration:**

ClinicalTrials.gov NCT03325699; https://clinicaltrials.gov/ct2/show/NCT03325699

**International Registered Report Identifier (IRRID):**

DERR1-10.2196/13711

## Introduction

### Background

The number of older adults in the population as well as their proportion within the total population are increasing in many parts of the world. In Europe, population aging has had and will continue to have major social and economic consequences. This is a fundamentally positive development where the added life span is of great benefit for both the individual and the society. Many older people are able to support themselves and continue to make important contributions to society. Yet, the risk for the individual to contract noncommunicable diseases and disability increases with age. This may impair the ability of the individual to live his/her life in the way that is desired. It also exerts pressure on health services and support systems for older people.

Cognitive conditions such as mild cognitive impairment (MCI) and dementia constitute a group of chronic diseases that predominantly affects older people [1]. The general increase in life span causes the number of people with MCI [2] to increase; people with dementia in Europe alone is estimated to reach 13.4 million by 2030. The challenge of ensuring a good life for all is likely to remain formidable [3]. Health care policies are focused on extending the ability of older people to continue to live independently as one way of meeting these challenges. As medical treatment options currently remain centered on symptomatic treatment, the use of technology [4] and specifically information and communication technologies (ICTs) is suggested as a way to support function and maintain a good life [5,6]. For people with neurocognitive disorders, a good quality of life (QoL) means that they experience a certain level of independence and self-management of daily-life activities, which may be promoted by using technology.

It is important to be aware of the heterogeneity in technology use abilities [7-9]. Involving end users in design and development of technology is especially important for the development of usable technology [10-12].

Cognitive problems affect both the individual as well as their surroundings [13,14]. Living together with and/or caring for a PwMCI or dementia can compromise the informal carer’s own well-being and health because of a feeling of being overloaded in the caregiving role [15-17].

The central role the informal carers play also accentuates the importance of the well-being of the informal carers themselves, and provision of support to the informal carers is therefore essential [18]. This is also an important target for the development of new supportive technologies. For example, people with dementia often experience disorientation and thus tend to get lost while they are outside on their own, causing stress for the caregiver. According to a pilot study by Pot et al [19], global positioning system tracking reduces feelings of worry when being alone outside, both in people with dementia as well as their caregivers. The Rosetta system integrated 3 ICT systems to support daily functioning (eg, social contact, memory, and activities) and to detect changes in daily behavior and identify emergency situations. Using this system, feelings of safety and security improved QoL in people with dementia and their carers [12].

Many devices and digital apps to support the day-to-day living activities at home for people with neurocognitive disorders have been developed during the recent years. However, most solutions focused on cognitive impairment training or support and safety for people living alone. Most of them are single apps or devices, but few were integrated into a single solution or product [20,21].

A recent study by Yousaf et al [22] categorized mobile health apps for dementia into apps for cognitive training and daily living (eg, word games, videos, and music), screening (eg, clock drawing), health and safety monitoring (eg, fall detection using installed cameras, alarms, and emergency help), leisure and socialization (eg, media for reminiscence therapy), and navigation (eg, tracking). Similarly, Meiland et al [11] looked at 3 fields of technologies for this group: (1) support with managing everyday life, (2) support with participating in pleasurable and meaningful activities, and (3) support with dementia health and social care provision. The study highlighted the importance of both inclusion of the group in the development of technology as well as the need for more comprehensive studies and higher quality evaluation of technology usability. Furthermore, the early introduction of technology in a degenerative cognitive process, or preferably before, may be an important factor [23,24].

The importance of including QoL as an outcome measure in dementia trials has been identified by the World Federation of Biological Psychiatry’s Old Age Taskforce [25] as well as others in the field. QoL is multifactorial; therefore, besides “the individual’s perception of their position in life in the context of culture and value systems in which they live, and in relation to their goals, standards, and concerns” [26,27], QoL also encompasses physical and mental health, social relationships, and participating in activities. In this trial, we therefore aim to analyze QoL in a broad sense.

Few systematic reviews are available that investigate the effectiveness of interventions on the QoL of people with dementia [11]. Among those available, 1 systematic review found preliminary evidence that nonpharmacological interventions targeting both patients and their carers improved the QoL of persons with dementia living at home [28]. In contrast, a systematic review of pharmacological interventions to improve QoL and well-being in persons with dementia found that these interventions failed to show positive results in these domains [25]. Other relevant systematic reviews focused on the use of assistive technologies to improve QoL in older people in general [29,30]. These covered technologies, including the computer and the internet (ie, general ICT), robotics, sensors, telemedicine, medication management apps, mobile tracking devices, and video games. Regarding QoL in older people with dementia specifically, the review [29] identified 3 studies investigating general ICT and sensors. These studies suggested that the investigated technologies have the capacity to enhance QoL not only in people with dementia but also in those caring for them. It is important to note that most studies included in these reviews were small, not randomized, did not include or report QoL as a primary outcome measure, or did not include a valid QoL measure [29]. Altogether, they state a current lack of high-quality evidence that these interventions improve the QoL of persons with neurocognitive disorders and underline the need of large randomized controlled trials (RCTs).

Results from a randomized controlled pilot study were published using a computerized platform entitled “A technology platform for the Assisted living of Dementia elderly Individuals and their informal carers” (ALADDIN) [31]. The authors demonstrated that the use of ALADDIN enhanced the carers’ ability to care for a person with dementia by improving the QoL and reducing distress and carer burden.

MCI and dementia are used mostly as terms in this text. Today, these conditions are more correctly referred to as neurocognitive disorders, classified according to diagnostic criteria in the fifth edition of the Diagnostic and Statistical Manual of Mental Disorders. However, as the earlier concepts, to a large extent, are still used in the literature, we have chosen not to continually change terms at all instances in this paper.

### Aim

In this trial, we aim to create a digital platform (Support Monitoring and Reminder for Mild Dementia, SMART4MD) to improve or maintain the QoL for people with mild neurocognitive disorders and their carers. The platform will provide the individual with reminders, information, and memory support in everyday life with the purpose of giving structure and lowering stress. In the trial, we will include participants with a diagnosed neurocognitive disorder as well as persons with an undiagnosed subjective memory problem and cognitive impairment, that is, 20 to 28 points on the Mini-Mental State Examination (MMSE). We will refer to this group as persons with mild cognitive impairment (PwMCI) in the following text.

### Primary Objective

The research hypothesis is that use of the SMART4MD app over a period of 18 months can result in an improvement in the QoL of PwMCI.

The statistical null hypothesis is that the use of the SMART4MD platform produces no change in the mean total Health-related quality of life Alzheimer's disease QoL-AD score of PwMCI over 18 months.

The statistical alternative hypothesis is that the use of the SMART4MD platform produces a change in the mean total QoL-AD score of PwMCI over 18 months.

### Secondary Objectives

The secondary objectives also apply to the intervention group using the app over a period of 18 months. The objectives are as follows:

To increase adherence to prescribed medication by 10% (all documented prescriptions)To reduce functional decline in PwMCI by 10% (as measured by Instrumental Activities of Daily Living)To monitor PwMCI’s attendance at health care appointments and admission to health care institutionsTo monitor the informal carers’ mental well-being as a strong determinant of caregiver burden and in turn of QoL of informal carers in the control and intervention group

## Methods

### Study Design

This is a pragmatic, multicenter RCT, and the Consolidated Standards of Reporting Trials (CONSORT) [32] guidelines will be followed. The ClinicalTrials.gov identifier is NCT03325699.

### Setting

This study will be performed in 3 European countries: Spain, Sweden, and Belgium and 4 participant centers, which are as follows: Consorci Sanitari de Terrassa (Catalonia, Spain), Servicio Andaluz de Salud (Andalusia, Spain), Blekinge Institute of Technology (Sweden), and University College Leuven-Limburg (Belgium).

### Participants

In total, 1200 participant dyads in 3 European countries (Spain, Sweden, and Belgium) will be included in the study. The participant dyads will comprise the PwMCI and his/her informal carer, with the PwMCI being the main participant. The participant will be selected by a nonprobabilistic consecutive sampling method. All participants will receive their treatment as usual (TAU) in their respective site, but the care of the intervention group will be improved with the support of the SMART4MD app.

### Sample Size

A total of 1200 dyads (PwMCI+carers) is the target for recruitment, divided over 2 groups: an intervention group, using the SMART4MD app, and a control group, not using the SMART4MD app. In this clinical trial, QoL is the primary outcome measure, measured by the QoL-AD total score [33]. This score is based on 13 four-point (1 to 4) items on a discrete visual analog scale. Recent papers [34] show the standard deviation (SD) of the total QoL-AD score approaches 7.

To detect a small effect size of 0.2 comparing 2 groups (intervention and control), using a 2-sided *t* test with a 5% statistical significance level, with a power of 80%, the minimum number of PwMCI required in each group is 394 (788 overall). If there would be a dropout rate of 20%, the number of PwMCI registered on the study would need to be 493 in each group (thus 986 overall).

On the other hand, one of our secondary objectives is to increase adherence to prescribed medication by 10% in the intervention group. If we consider that in people with dementia, the treatment adherence is between 44% and 99% [35,36], and assuming the less prevalence (44%), which we want to increase by 10%, with a power of 0.8 and a significance level of .05, we need 1174 subjects (20% dropouts included). Therefore, the sample size of this study is adequate to detect statistical and clinical differences between groups for the QoL-AD (primary outcome) and treatment adherence (a secondary outcome).

### Inclusion Criteria

A participant will be eligible for inclusion in this trial only if all of the following criteria are met:

Participants score 20 to 28 points on the MMSE whether or not a diagnosed neurodegenerative disease is present;A professional assessment of the patient's own experience of memory problems over a substantial period of time (more than 6 months);Participants are older than 55 years;Participants are home care recipients;Participants have an informal carer;Participants take prescribed medication and are in charge of their own medication use;Participants have no specific conditions reducing their physical ability to use the app, for example, visual, hearing, or motor impairments.

### Exclusion Criteria (Persons With Mild Cognitive Impairment Only)

A participant will not be eligible for inclusion in this trial if any of the following criteria apply:

Participants have a terminal illness with less than 3 years of expected survival;Participants score above 11 on the Geriatric Depression Scale (GDS-15) [37] or have another known significant cause of disease as an explanation for cognitive impairment such as abuse and other psychiatric diagnoses such as bipolar disorders, schizophrenia, and developmental disorders.

### Recruitment

Participants will be identified from a cohort of people with cognitive impairment that has been present for more than 6 months and who meet all the study eligibility criteria. Participants can be under primary care services as well as secondary care services, such as those who are being followed up in memory clinics, outpatient clinics, day hospitals or other components of specialist mental health care, geriatric medicine, and neurology services. Participants will also be identified from patient databases such as those integrated in the centers’ networks. The identification process will consist of screening using information gathered from medical notes, clinic records, and/or clinical consultations for initial eligibility based on inclusion criteria.

Each country will have a country specific recruitment plan that will be revised by the trial steering committee.

After a brief explanation of the study design and research goals, participants will be invited to participate in the study, and an appointment with the researchers will be made. Participants will be provided with all the information they need to make an informed decision via a participant information sheet. They will be given a cooling-off period of at least 24 hours between informally agreeing to participate in the study and being invited to formally consent in a meeting with the research team.

At the first visit, the researcher will explain the study in detail and answer any questions the patient or caregiver may have. The patient’s eligibility will be confirmed and their ability to consent will be assessed. Once consent is officially given by signing an informed consent form by all parties, the dyad will be randomized into either the intervention or the control group.

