### Follow-Up Visits

There will be 3 follow-up visits at 6, 12, and 18 months after baseline interview. A summary of visits’ assessments is shown in Table 1. In addition, to measure medication adherence, there will be a preadherence phone call in each follow-up visit (30 days before the visit).

**Table 1 table1:** Schedule of events.

Events, assessments, and data collection	Screening	Baseline	Tablet delivery	Month 6 ±18 days	Month 12 ±18 days	Month 18 ±18 days
Informed consent (PwMCI^a^ and informal carer)	X^b^	—^c^	—	—	—	—
Review of inclusion and exclusion criteria (PwMCI)	X	—	—	—	—	—
Demography (PwMCI and informal carer) and medical history (PwMCI)	—	X	—	—	—	—
Introduction and training for Support Monitoring and Reminder for Mild Dementia (intervention group only, PwMCI and informal carer)	—	—	X	—	—	—
Geriatric Depression Scale (PwMCI)	X	—	—	X	X	X
Mini-Mental State Examination (PwMCI)	X	—	—	X	X	X
Quality of Life in Alzheimer's Disease scale (PwMCI)	—	X	—	X	X	X
Instrumental Activities of Daily Living (PwMCI)	—	X	—	X	X	X
Adherence to prescribed medication (PwMCI)	—	X	—	X	X	X
EuroQol-5D (PwMCI and informal carer)	—	X	—	X	X	X
Attendance at appointments and admissions (PwMCI)	—	X	—	X	X	X
Familiarity with tech survey (PwMCI and informal carer)	—	—	X	—	—	—
QoL-AD on behalf of PwMCI (informal carer)	—	X	—	X	X	X
Zarit Caregiver Burden Interview (informal carer)	—	X	—	X	X	X
User satisfaction survey (intervention group only, PwMCI, and informal carer)	—	—	—	X	X	X
User behavior (intervention group only, informal carer, and PwMCI)	—	—	—	X	X	X

^a^PwMCI: persons with mild cognitive impairment.

^b^The instrument is used at this time point.

^c^The instrument is not used at this time point.

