#### Primary Outcome Analysis

The primary analysis will be the comparison of total QoL-AD score mean changes (at 18 months) between intervention group and control group using a 2-sample, 2-sided Monte Carlo permutation *t* test. The use of a permutation test will avoid the need for strong assumptions about the distribution of the data. Similarly, a bootstrap approach will be used to obtain the 95% confidence limits for the difference between the group means.

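### The stated trigger for randomization is signed consent, not completed baseline assessment, so baseline QoL-AD ratings may be made with allocation known

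*Protocol article*

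**What the plan says.** The Recruitment section sets out the first visit in order. It opens with "At the first visit, the researcher will explain the study in detail and answer any questions the patient or caregiver may have". Eligibility is then confirmed and capacity to consent assessed, after which comes "Once consent is officially given by signing an informed consent form by all parties, the dyad will be randomized". No baseline measurement is mentioned between consent and allocation.

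Table 1 (Follow-Up Visits) has the columns Screening, Baseline, Tablet delivery, and months 6, 12 and 18:

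- Consent and the eligibility review are marked under Screening only. The depression scale and the MMSE have their first assessment there.
- The rows "Quality of Life in Alzheimer's Disease scale (PwMCI" and "QoL-AD on behalf of PwMCI (informal carer" are blank under Screening and first marked under Baseline. The same holds for IADL, EQ-5D, medication adherence and the Zarit interview.
- The row "Introduction and training for Support Monitoring and Reminder for Mild Dementia (intervention group only, PwMCI and informal carer" is marked under Tablet delivery.
- There is no row for randomization.

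The Primary Outcome Analysis section defines the primary contrast as the "comparison of total QoL-AD score mean changes (at 18 months". The Adjusted Analyses section adds an analysis of covariance with baseline QoL-AD as the covariate. The Randomization section says that investigators cannot see the sequence, but not when a dyad's assignment is made or disclosed.

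**The concern.** QoL-AD is a subjective measure, obtained by interview from the person with mild cognitive impairment and by self-completion from the carer. The control is usual care without a sham device, and no masking of participants, carers or interviewers is described. Keeping the list from investigators protects the assignment before it is made. It does not hide an assignment already made.

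If the dyad or the interviewer knows the allocation when the baseline questionnaire is completed, expecting a tablet, or knowing that none is coming, could move baseline ratings differently in the two arms. That difference would then be part of the primary change score, although it is neither a chance imbalance nor an effect of using the app.

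There is a second route. A dyad that leaves after randomization but before baseline has no change score, although the analysis is meant to follow intention to treat. The 20% dropout allowance protects power against such losses. It does not protect comparability if the losses differ by arm.

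**Working it through.** **1. Order of events.** Recruitment makes signed consent the condition for randomization. Table 1 puts consent under Screening and QoL-AD under the later Baseline column. Together these give: consent (Screening), randomization, baseline QoL-AD (Baseline), tablet. The order consent, baseline, randomization, tablet is compatible with the table but is stated nowhere.

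**2. The plan's own figure.** Inputs from Sample Size: standardized effect 0.2, two-sided 5% level, 80% power, SD about 7, 20% dropout.

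- Normal approximation: n = 2(1.960 + 0.842)² / 0.2² = 392.4, so 393 per group.
- Noncentral t: 393.4, so 394 per group, as stated.
- Dropout: 394 / 0.8 = 492.5, so 493 per group and 986 overall, as stated.
- Design difference in points: 0.2 × 7 = 1.4.

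No input depends on when baseline is taken, so correcting the order leaves these figures unchanged.

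**3. How a baseline shift enters the analyses.** Let knowledge of allocation shift one arm's mean baseline rating by b points and leave the 18-month rating unaffected.

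- Change score: the between-arm difference in change moves by b.
- Analysis of covariance: the adjusted difference moves by ρ × b, where ρ is the baseline to 18-month correlation and the two variances are assumed equal. With ρ = 0.5 (assumed) and b = 0.5, this is 0.25 points. Adjustment reduces the shift but does not remove it.
- 18-month score alone: moves by 0, because baseline is not used.

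**4. Illustration.** The values of b are assumed, since the documents give none. With 394 analysed per group, SE = SD × √(2/394), which is 0.499 for an SD of change of 7 (assumed equal to the stated score SD) and 0.356 for an assumed SD of 5.

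- Type I error = Φ(−1.96 − b/SE) + 1 − Φ(1.96 − b/SE).
- Power when the shift works against a true 1.4-point effect = Φ((1.4 − b)/SE − 1.96).

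| b (points) | b / 1.4 | Type I error, SD 7 | Type I error, SD 5 | Power if masking, SD 7 |
|---|---|---|---|---|
| 0 | 0% | 5% | 5% | 80% |
| 0.25 | 18% | 8% | 11% | 64% |
| 0.5 | 36% | 17% | 29% | 44% |
| 1.0 | 71% | 52% | 80% | 12% |

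The table shows sensitivity, not an estimate of what happened. Because the target effect is small, small shifts matter.

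**The case against.** The strongest reply is that the text does not fix the order. The word once makes consent a precondition; it does not say that randomization is immediate or precedes baseline. Recruitment is a summary that names no baseline instrument, so its silence between consent and allocation is weak evidence. Table 1 has no randomization row, and its first event restricted to one arm comes after Baseline, which fits allocation between Baseline and Tablet delivery. An article may also leave workflow detail to the full protocol.

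Much of this stands, and it limits the claim. A reader might infer that dyads were randomized the moment consent was signed, or that the baseline QoL-AD was rated with allocation known. The documents support neither as fact: immediacy is not stated, and nor is the time at which the assignment reaches the dyad or interviewer. A reader might also take 0.5 points as the expected bias; that figure is assumed. The direction is open too: a shift that raises the intervention arm's baseline would count against the app.

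What does not stand is treating this as detail left out of an article. The article gives an explicit sequence and an explicit trigger, and the trigger is consent alone. A site following it would allocate before the baseline questionnaires.

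**Conclusion.** The point holds in this form: as written, signed consent triggers randomization, baseline QoL-AD falls under a later column, and nothing secures baseline first, so baseline ratings may be made with allocation known. This matters because baseline enters the primary change contrast with full weight and the planned covariance adjustment uses the same score.

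The possible bias is b points for a one-arm shift of b, against a 1.4-point design difference. That rests on three assumptions: the sites follow the order as written, the assignment is known by the baseline interview, and the reaction affects the baseline rating but not the 18-month one. None can be confirmed from the article. If randomization in practice followed baseline, the wording needs correcting but the data are not affected in this way.

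**What to change.** - **Text.** In Recruitment and Randomization, state that the web-based system releases an allocation only after eligibility is confirmed and all baseline assessments, including both QoL-AD ratings, are completed and locked.
- **Table 1.** Show randomization between Baseline and Tablet delivery.
- **Dyads already enrolled.** Recruitment was expected to end in February 2019 and the article appeared in June 2019, so a new release rule may reach few or none of them. Compare randomization time stamps with baseline dates for every dyad, and report the order by site and arm, along with the number lost between the two events.
- **If baselines followed randomization.** Add a sensitivity analysis comparing 18-month QoL-AD between arms without the baseline score. This is better than excluding the affected dyads, which could remove most of the trial. With SD 7 and 394 analysed per group, it has the 80% power for 1.4 points that the Sample Size section calculates. It does not address knowledge of allocation at the 18-month rating itself.

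The cost is a sentence, a table row, a date comparison and at most one further analysis. Allocation waits until baseline is complete, and the sample size is unchanged.
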